### **9.1 Grading System**

AE severity grading is described in Section 8.3.1.

### **9.2 Dose Modification Instructions**

No dose modifications will be permitted in this study.

### **9.3 General Criteria for Permanent Discontinuation of Study Medication**

A participant will be permanently discontinued from medication use by the physician investigators for any of the following reasons, according to the HCV treatment guidelines:

- 5-fold or greater increase in ALT or AST at the PK1 or PK2 visit compared to baseline result (Screening visit), confirmed by immediate repeat testing
- Any increase of ALT or AST of less than 5-fold from baseline (Screening visit) at the PK1 or PK2 visit that is accompanied by any weakness, nausea, vomiting, or jaundice
- 3-fold or greater increase in ALT or AST accompanied by bilirubin >2x the upper limit of normal, confirmed on immediate repeat testing
- Increase HCV RNA viral load by greater than 10-fold at PK2 visit (6-8 weeks after starting treatment)
- Participant is unable or unwilling to comply with required study procedures
- If the participant delivers prematurely (and is still on study medication) and desires to breastfeed
- Participant might be put at undue risk to their safety and well-being by continuing medication use, according to the judgment of the study investigators. The study investigators will consult with the independent safety physician prior to all study medication discontinuation instituted for this reason.

Any time a participant is permanently discontinued from study medication (prior to completion of the 12 week course of study medication), HCV resistance testing will be performed.

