## 5.3 Exclusion Criteria

Women who meet any of the following criteria will be excluded from the study:

- 1) Participant report of any of the following at Screening or Enrollment:
  - a. Previous treatment for Hepatitis C virus with sofosbuvir or a NS5A inhibitor

- b. Use of any medications contraindicated with concurrent use of ledipasvir or sofosbuvir according to the most current HARVONI package insert
  - c. Plans to relocate away from the study site area in the next 1 year and 4 months
  - d. Current sexual partner is known to be infected with HIV or Hepatitis B virus
  - e. History of cirrhosis documented by previous liver biopsy or liver imaging tests
- 2) Reports participating in any other research study involving drugs or medical devices within 60 days or less prior to Enrollment
- 3) Clinically significant and habitual non-therapeutic drug abuse, not including marijuana, as determined by Protocol Chair
- 4) At Screening or Enrollment, as determined by the Protocol Chair, any significant uncontrolled active or chronic cardiovascular, renal, liver (such as evidence of decompensated cirrhosis by ascites, encephalopathy, or variceal hemorrhage), hematologic, neurologic, gastrointestinal, psychiatric, endocrine, respiratory, immunologic disorder or infectious disease (other than Hepatitis C)
- 5) Has a high risk of preterm birth defined as a history of spontaneous preterm birth at less than 34 weeks of gestation or a shortened cervical length of less than 20 millimeters
- 6) Has any of the following laboratory abnormalities at Screening:
  - a. Aspartate aminotransferase (AST) or alanine transaminase (ALT) greater than 10 times the upper limit of normal
  - b. Hemoglobin less than 9 g/dL
  - c. Platelet count less than 90,000 per mm^3
  - d. International normalized ratio (INR) > 1.5
  - e. Creatinine greater than 1.4
  - f. Medical history of cirrhosis
- 7) Has any other condition that, in the opinion of the IRB/designee, would preclude informed consent, make study participation unsafe, complicate interpretation of study outcome data, or otherwise interfere with achieving study objectives.

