## 7.5 Follow-up Procedures for Participants Who Permanently Discontinue Study Medication

Participants will be permanently discontinued for significant laboratory abnormalities or adverse events as outlined in section 9.3 and 9.4, if they miss greater one dose per week (averaged over the duration of the study), or if they choose to discontinue the study medication. Participants who are permanently discontinued from the study will be instructed to return the study medication and study medication log. All protocol-specified study procedures will continue for safety except the following:

- Provision of study medication
- Provision of medication use adherence counseling

The following procedures will be performed at the visit in which study medication use is permanently discontinued:

- Collection of blood for PK analysis (single time point)
- HCV resistance testing
- Viral load as needed (i.e. participant withdraws, investigator opinion)
- Medical history review
- Concomitant medication review
- Brief physical examination including vital signs, if indicated.

The participant will be asked to continue in the study and complete all remaining scheduled maternal and infant visits per protocol for safety.

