### **8.3 Adverse Events Definitions and Reporting Requirements**

#### **8.3.1 Adverse Events**

An AE is defined as any untoward medical occurrence in a clinical research participant administered an investigational medication and which does not necessarily have a causal relationship with the investigational medication. As such, an AE can be an unfavorable or unintended sign (including an abnormal laboratory finding, for example), symptom or disease temporally associated with the use of an investigational medication, whether or not considered related to the medication. The term “investigational medication” for this study refers to the study medication.

Study participants will be provided instructions for contacting the study site to report any untoward medical occurrences they may experience throughout their participation in the study. Participants receiving prenatal care and/or delivering at Magee-Womens Hospital will be instructed to come to Magee-Womens Hospital if they experience any adverse events requiring evaluation. Participants will be seen by a physician investigator/study clinician. If the participant is not receiving care at Magee-Womens Hospital, then they will be instructed to seek medical care with their local primary care physician/obstetrical team. Close communication with the participant and the primary care provider/obstetrical team will be maintained. Participants may have an unscheduled visit with the physician investigator/study clinicians as necessary or desired. In cases of potentially life-threatening events, participants will be instructed to seek immediate emergency care. With appropriate permission of the participant, whenever possible, records from all non-study medical providers related to untoward medical occurrences will be obtained and required data elements will be abstracted and recorded on study CRFs. All participants reporting an untoward medical occurrence will be followed clinically until the occurrence resolves (returns to baseline) or stabilizes.

Study site staff will document all AEs reported by or observed in enrolled study participants regardless of severity and presumed relationship to investigational medication, including gradable laboratory findings. AE severity will be graded per the DAIDS Table for Grading Adult and Pediatric Adverse Events, Version 1.0, December 2004 (Clarification dated August 2009).

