### **8.3.3 Adverse Event Relationship to Study Medication**

Relatedness is an assessment made by the physician investigator of whether or not the event is related to the study agent.

- *Related:* There is a reasonable possibility that the AE may be related to the study agent(s)
- *Not Related:* There is not a reasonable possibility that the AE is related to the study agent(s)

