##### **Grade 3**

For participants who develop a Grade 3 AE as defined by the DAIDS Table for Grading Adult and Pediatric Adverse Events, Version 1.0, December 2004 (Clarification dated August 2009) that is judged by the study investigators to be unrelated to study medication, the study medication will continue. The study medication must be permanently discontinued for participants who develop a Grade 3 AE judged by a physician investigators to be related to the study medication.

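### A Grade 3 ALT/AST rise that meets a hepatic stopping criterion in Section 9.3 but is judged unrelated is literally ordered to continue drug by Section 9.4, and no text expressly removes that order

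*Protocol*

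**What the plan says.** Section 9.3 opens: "A participant will be permanently discontinued from medication use by the physician investigators for any of the following reasons". Its hepatic criteria are:

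- "5-fold or greater increase in ALT or AST at the PK1 or PK2 visit compared to baseline result (Screening visit), confirmed by immediate repeat testing";
- a smaller ALT/AST rise at PK1 or PK2 with any of the symptoms it names, with no repeat test required;
- "3-fold or greater increase in ALT or AST accompanied by bilirubin >2x the upper limit of normal, confirmed on immediate repeat testing".

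None of the three asks whether the rise was caused by the drug.

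Section 9.4 sorts adverse events by grade and relatedness. Under Grade 3, for an event "judged by the study investigators to be unrelated to study medication, the study medication will continue"; a related Grade 3 event must stop drug.

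Section 8.3.1 has staff record adverse events "regardless of severity and presumed relationship to investigational medication, including gradable laboratory findings". Section 8.3.3 then requires a two-way call, related or not related.

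Section 7.5 refers to both sections: "Participants will be permanently discontinued for significant laboratory abnormalities or adverse events as outlined in section 9.3 and 9.4".

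**The concern.** A transaminase rise is both a 9.3 criterion and, through Section 8.3.1, an adverse event governed by 9.4. Once the investigator marks a Grade 3 rise as not related, the two sections give opposite dosing instructions for the same result. Whichever the site follows, it departs from a written order.

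The choice matters both ways. Section 13.3.1 says there are no studies of this drug in pregnant women, so dosing on through a liver signal has unknown risk. The same section warns that an incomplete course may lead to viral resistance, so stopping has a cost too.

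The choice also affects the data. The Protocol Summary replaces women who do not complete treatment, and Section 10.5.2 leaves them out of the SVR12 analysis. A woman in the overlap is therefore kept or replaced according to which sentence the clinician applied.

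A statistical analysis plan would not settle this, because it is a dosing rule for the clinic.

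**Working it through.** The protocol gives no figure to reproduce. The check compares the texts, then asks whether the overlap can be reached.

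**1. The rules side by side**

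| Situation | Section 9.3 | Section 9.4 |
|---|---|---|
| Hepatic criterion met, Grade 1 or 2 | Stop | Continue, but only as a general rule |
| Hepatic criterion met, Grade 3, related | Stop | Stop |
| Hepatic criterion met, Grade 3, not related | Stop | Continue, with no qualifier and no exception for 9.3 |
| Hepatic criterion met, Grade 4, related | Stop | Stop |
| Hepatic criterion met, Grade 4, not related | Stop | Silent |

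Only the third row has two direct orders that oppose each other. The Grade 4 paragraph shows how 9.4 reads when it means only to list a ground for stopping: it says nothing about unrelated events. The Grade 3 paragraph gives a positive instruction instead.

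**2. Can a 9.3 rise be Grade 3?**

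The cut-offs are in the external grading table. Assume Grade 3 runs from L to U times the upper limit of normal (ULN), and let b be the Screening value in multiples of ULN.

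- A rise of exactly k-fold is Grade 3 when L/k ≤ b ≤ U/k. For an illustrative L = 5 and U = 10: k = 5 gives b from 5/5 = 1 to 10/5 = 2, and k = 3 gives b from 5/3 = 1.7 to 10/3 = 3.3.
- For a rise of k-fold or more, only the upper limit b ≤ U/k binds:

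| Assumed U | 5-fold or more: b up to | 3-fold or more: b up to |
|---|---|---|
| 8 | 8/5 = 1.6 | 8/3 = 2.7 |
| 10 | 10/5 = 2.0 | 10/3 = 3.3 |
| 20 | 20/5 = 4.0 | 20/3 = 6.7 |

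- For the criterion of a rise below 5-fold with symptoms, with L = 5 and U = 10, b must exceed 5/5 = 1 and be below 10.

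Section 5.3 excludes only "Aspartate aminotransferase (AST) or alanine transaminase (ALT) greater than 10 times the upper limit of normal". All of these Screening values are therefore eligible, and the overlap can occur across the assumed range.

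**3. How much drug separates the two orders?**

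Inputs from Table 1: start at 23+0 to 24+6 weeks; PK1 at 25+0 to 26+6 and at least 10 days after start; PK2 at 29+0 to 30+6; course of 12 × 7 = 84 days.

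- PK1: earliest day 10 (the minimum), latest 23+0 to 26+6 = day 27. Remaining: 84 − 27 = 57 to 84 − 10 = 74 days.
- PK2: earliest 24+6 to 29+0 = day 29, latest 23+0 to 30+6 = day 55. Remaining: 84 − 55 = 29 to 84 − 29 = 55 days.

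These are nominal figures only. Table 1 calls the PK windows targets that may be missed without a deviation. The count ignores time for repeat testing and any later stop on other grounds. The 3-fold criterion is not tied to PK1 or PK2, so these days do not bound it.

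**4. How often?**

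The protocol gives no rate for ALT/AST rises. Sections 2.4.1 and 13.3.1 report bilirubin above 1.5 times ULN in under 1% of those treated for 12 weeks, none of them pregnant. If that carried over, fewer than 15 × 0.01 = 0.15 women would be expected, before requiring bilirubin above 2 times ULN, a 3-fold ALT/AST rise, Grade 3 and an unrelated call. This concerns one criterion only, and its transfer to pregnancy is an assumption.

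**The case against.** The best defence is that the two sections add to each other. Section 9.3 lists grounds each of which is enough. Section 9.4, on this view, says only when grade and relatedness are themselves a ground, so an unrelated Grade 3 event is not by itself a reason to stop. Section 7.5 supports this: it names laboratory abnormalities beside adverse events and cites both sections as grounds for stopping. The literal reading also proves too much, since an unrelated Grade 3 event would then cancel the stops for breastfeeding after preterm delivery or for non-compliance. This is the more sensible reading and probably the intended one. But the text does not state it, and in the hepatic case the same laboratory value is both the criterion and the adverse event.

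A reader might infer that the conflict is wholly unqualified and ties the clinician's hands. The protocol does not support that. The opening of Section 9 sets a general risk-benefit standard with consultation of the independent safety monitor, the last criterion in 9.3 allows a stop for undue risk, and Sections 8.1 and 8.2 provide monthly and ad hoc independent review. A worried clinician has authority to stop. What is missing is a sentence saying that a fixed hepatic threshold holds once the event has been called unrelated.

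The unrelated call may also be uncommon. Section 8.3.3 treats any reasonable possibility as related, and a related Grade 3 event stops under 9.4 as well, so the sections usually agree. Section 2.1 does link hepatitis C in pregnancy with intrahepatic cholestasis, a possible alternative cause, but it says nothing about transaminase rises of this size.

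**Conclusion.** The contradiction is real but narrow. For an ALT/AST rise that meets any of the three hepatic criteria in 9.3, is Grade 3 and is judged unrelated, 9.3 orders a permanent stop and the literal Grade 3 sentence in 9.4 orders continuation. Section 7.5 favours 9.3, and other text leaves room for judgement, but none of it removes the order to continue.

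That the overlap can occur rests on assumed Grade 3 limits (upper edge 8 to 20 times ULN). A reader might take the 29 to 74 days from the nominal windows, about 35% to 88% of the course, as the size of the problem. The protocol does not support that: the windows are targets, and one criterion is not tied to them. The frequency is likewise unknown and probably low in 15 women. This is a drafting fault in a safety rule, worth correcting because it concerns dosing in pregnancy and costs almost nothing. It does not put the primary PK analysis or the sample size in doubt.

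**What to change.** Amend the Grade 3 sentence in Section 9.4 so that study medication continues after an unrelated Grade 3 adverse event unless a criterion in Section 9.3 is met, in which case 9.3 applies regardless of judged relationship.

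This leaves the 9.3 thresholds, the consultation with the safety monitor and the handling of all other grades unchanged. The cost is one added clause, with no new tests, visits or participants.

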## **9 CLINICAL MANAGEMENT**

Guidelines for clinical management and permanent discontinuation of study medication are outlined in this section. In general, the physician investigators will only discontinue study medication in consultation with the independent physician safety monitor if they feel that the risk of study medication continuation outweighs the benefits of study medication continuation. The physician investigators will document all permanent discontinuations on applicable CRFs.

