#### **9.4 Permanent Discontinuation in Response to Adverse Events**

##### **Grade 1 or 2**

In general, a participant who develops a Grade 1 or 2 AE as defined by the DAIDS Table for Grading Adult and Pediatric Adverse Events, Version 1.0, December 2004 (Clarification dated August 2009) regardless of relationship to study medication will continue study medication use.

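### Section 9.3 stops medication at once for a symptomatic ALT/AST rise below 5-fold, but asks for a confirming repeat when the symptomatic rise is 5-fold or more

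*Protocol*

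**What the plan says.** Protocol section 9.3 lists reasons for permanent discontinuation, any one of which is enough. Three concern liver enzymes:

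- **First criterion.** An ALT or AST rise of at least 5-fold at PK1 or PK2, "compared to baseline result (Screening visit), confirmed by immediate repeat testing". It makes no exception for symptoms.
- **Second criterion.** "Any increase of ALT or AST of less than 5-fold from baseline (Screening visit) at the PK1 or PK2 visit", provided the woman also has at least one of four symptoms: jaundice, vomiting, nausea or weakness. No repeat is required.
- **Third criterion.** "3-fold or greater increase in ALT or AST accompanied by bilirubin >2x the upper limit of normal, confirmed on immediate repeat testing".

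Other routes to a stop need no repeat test:

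- Section 9.3 also has a discretionary criterion: "Participant might be put at undue risk to their safety and well-being by continuing medication use, according to the judgment of the study investigators". It requires prior consultation with the independent safety physician.
- Section 9.4 requires a stop for a Grade 3 or Grade 4 event judged related. Section 8.3.3 sets a low bar for relatedness, a reasonable possibility.
- For Grade 1 or 2 events, section 9.4 says that in general a participant "regardless of relationship to study medication will continue study medication use".

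The opening of section 9 presents all of this as guidance: "In general, the physician investigators will only discontinue study medication in consultation with the independent physician safety monitor".

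**The concern.** A stopping rule for liver injury should not become harder to meet as the injury signal grows. Here the symptom criterion has an upper limit, so it switches off where the enzyme rise becomes large. Above that limit a symptomatic woman is handled like one without symptoms, and the mandatory stop waits for a repeat. The current text of section 9 gives no interim hold while the repeat is pending, although the table of contents still names a temporary hold in the title of 9.3.

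At stake is the clarity of a participant-safety rule for a drug with which section 2.5 reports no experience in pregnant women. Whether a symptomatic woman takes further doses before the repeat result is known would depend on individual judgment.

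**Working it through.** There is no figure in the plan to reproduce, so the check applies the three liver criteria to cases on either side of the 5-fold line. The fold values are illustrative.

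**Step 1: the criteria as rules.** Let *f* be the ALT or AST value divided by the Screening value.

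- First: *f* ≥ 5 gives a stop after one confirming repeat.
- Second: 1 < *f* < 5 with a listed symptom gives a stop on the first result.
- Third: *f* ≥ 3 with bilirubin above twice the upper limit of normal gives a stop after one confirming repeat.

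**Step 2: repeats needed before a liver criterion is met.**

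| Case | Criterion that applies | Repeats, current text | Repeats, cap deleted |
|---|---|---|---|
| 1.5-fold, nausea | second | 0 | 0 |
| 4.9-fold, jaundice | second | 0 | 0 |
| 5.0-fold, jaundice | first | 1 | 0 |
| 5.0-fold, jaundice, bilirubin > 2x ULN | first and third | 1 | 0 |
| 5.0-fold, no symptoms | first | 1 | 1 |

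The same pattern held over fold values from 1.1 to 20, with and without symptoms and with and without raised bilirubin. Only the symptomatic cases at 5-fold or more change when the cap is deleted.

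**Step 3: what the repeat then decides.** Take a symptomatic woman whose first result is 5-fold or more.

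- Repeat 5-fold or more: the first criterion is confirmed and medication stops.
- Repeat above baseline but below 5-fold: the second criterion applies on a literal reading and medication stops.
- Repeat at or below baseline: no liver criterion is met.

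The usual cost of the current wording is therefore the time taken by one immediate repeat. One ambiguity remains in the middle case, because the second criterion is tied to a rise at the PK1 or PK2 visit and the text does not say whether a later repeat counts as that visit. Suppose it does not, and bilirubin is not raised. A woman at 5.2-fold whose repeat is 4.7-fold then meets no liver criterion, while a woman at 4.7-fold on the first draw must stop.

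**Step 4: how often the rule is applied.** Table 5 schedules on-treatment hepatic panels only at PK1 and PK2. With 15 women, that is 15 x 2 = 30 planned checks. Section 5.1.2 foresees at most two replacements, so the upper figure is (15 + 2) x 2 = 34. These are opportunities for the rule to apply, not expected events. The documents give no frequency for a symptomatic 5-fold rise. The DAIDS grading table is not reproduced in them, so the share already caught by section 9.4 could be anywhere from none to all.

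**The case against.** The strongest reply is that the wording changes almost no outcome. As Step 3 shows, the repeat nearly always leads to a stop, and the exception is a repeat at or below baseline, which suggests a spurious first value. Confirming a large value before an irreversible step is defensible, because section 13.3.1 warns that an incomplete course may lead to resistance and limit later treatment. An investigator who is worried can stop the same day under the undue-risk criterion, which needs no grade, no relatedness judgment and no repeat. This is a single-site trial in which discontinuations generally go through the independent monitor, so divergent handling is less likely. The criteria are also attributed to treatment guidelines that are not in the documents, so it cannot be checked whether the proposed wording would depart from them.

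Most of this stands, and it is why the point is minor. It does not remove the inversion. The undue-risk criterion is discretionary, and section 9.4 depends on grade and relatedness, so neither is triggered by a symptomatic 5-fold rise as such. The argument for confirming first would apply at least as well to smaller symptomatic rises, where the plan requires no confirmation.

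**Conclusion.** The concern holds as a small defect in a stated safety rule. Read literally, the liver criteria of section 9.3 ask for one repeat test before a mandatory stop in a symptomatic woman with a rise of 5-fold or more, and for none when her rise is smaller. The gap remains where section 9.4 does not already force a stop, that is, for events below Grade 3 and for events not judged related, and where the undue-risk criterion is not used.

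The usual consequence is a short delay and some room for inconsistent handling while the repeat is pending. The size in participants cannot be estimated from the documents. No endpoint, analysis or sample size depends on it. The conclusion assumes that each criterion is applied as written, in particular that the cap on the second one is meant literally. The point is worth correcting at the next amendment, and confidence that it matters in practice is moderate.

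**What to change.** In the second liver criterion of section 9.3, delete the four words that cap the rise (of less than 5-fold). Any ALT or AST rise from Screening at PK1 or PK2 with a listed symptom then meets the same criterion on the first result. The first criterion, with its confirming repeat, is left to govern rises of 5-fold or more without symptoms.

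The cost is a one-line wording change, with no added tests, visits or participants. The downside is that a spuriously high value in a woman with symptoms would lead to a permanent stop before 12 weeks, with the resistance risk described in section 13.3.1. The plan already accepts that for smaller symptomatic rises. Adding a repeat to the second criterion would also remove the inversion, but by delaying the stop for every symptomatic rise below 5-fold, which weakens the existing rule.
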